### Statistical analysis

2.9.

In accordance with intention-to-treat, all 60 participants randomized in stage 1 will be included in all analyses. We will summarize participant characteristics at baseline using means and standard deviations (or medians and interquartile ranges) for continuous variables and frequencies and percentages for discrete variables. We will summarize the distribution of FI and secondary outcomes at baseline, 3 months, and 6 months. Our approach to handling incomplete or missing data will depend on the causes and amount. We will determine the likely reasons for missing data (ignorable or not ignorable) and use appropriate methods to address those reasons (e.g., multiple imputation for ignorable). We will use a time-ordered conditional imputation strategy specifically designed for SMART data if we perform multiple imputation [51].

For Aim 1, we will use descriptive statistics to summarize the feasibility (proportion of eligible patients who enrolled). We will also assess the change in FI, dietary intake, food expenditures, psychological outcomes, and healthcare use based on survey responses and EHR data extraction at baseline and 3 months. Given our small sample size, we do not expect to see significant differences in outcomes between participants who were randomized to WIC referral versus those randomized to WIC referral + navigation. Although not the goal or expected, a sample size of 60 does provide sufficient power (0.9) to detect a 2-point difference (SD: 2.0) between the 2 arms with an alpha of 5 % and assuming up to a 25 % loss to follow-up (22 participants per group) using a two-sample *t*-test.

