For Aim 2, participants who have a suboptimal improvement in FI (<2-point) at 3 months will be re-randomized in stage 2 resulting in four embedded adaptive interventions (Table 3). To evaluate change in outcomes over time across the four adaptive interventions in the SMART design, piecewise (segmented) marginal mean regression models (fit using generalized estimating equations (GEE)) will be used [52]. In this pilot study, we do not expect to see significant differences between interventions given our small sample size. We will use descriptive statistics and two-stage piecewise GEE regression models to assess differences in outcomes. The fit of this model to our data will inform estimates of variance and the correlation matrix that are necessary to conduct piecewise regression models to assess the differences in a future, fully-powered SMART.

For Aim 3, the semi-structured interviews will occur via telephone and be digitally recorded and transcribed (and translated), with identifying data removed, and guided by a semi-structured interview guide. The guide will be based on the RE-AIM framework. Analyses will be conducted by 2 trained staff, working in parallel, guided by the constant comparison method, and informed by grounded theory methodologies [53–56]. This approach is well suited for systematically uncovering participant experiences and comparing them within and across groups. Analytic steps will include: 1) after each interview, interviewers will document field notes; 2) transcripts and field notes will be entered into Atlas.ti software (Berlin, Germany) for coding and analysis; 3) we will develop a preliminary codebook to include pre-determined deductive codes and inductive codes that emerge from the data; 4) coding differences will be discussed and negotiated until consensus is reached and high inter-rater reliability (k ≥ 0.80) is achieved; 5) similarities and differences will be examined and themes developed; 6) we will “member check” themes to refine and establish the validity of the results. From these rich data, we will gain a greater understanding of how and why interventions produced the outcomes they did and develop a conceptual understanding of how interventions to address FI can most effectively improve care for pregnant patients.

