Gestational Diabetes Mellitus (GDM)	One-step oral glucose tolerance test shows ≥2 abnormal values consistent with diagnostic criteria for GDM [58], or incident diagnosis of GDM added during pregnancy	EHR data extraction	6
Glucose Homeostasis (Hypo or Hyperglycemia, glucose variability)	14-day monitoring of glucose for episodes of hypo/hyperglycemia and glucose coefficient of variation	CGM	0, 6
Excess Gestational Weight Gain	If pre-pregnancy BMI ≥30, gaining ≥20lbs; if BMI 25–29.9, gaining ≥25lbs; if BMI <25, gaining ≥35lbs [59]	EHR data extraction	Post-delivery
Pre-eclampsia	Incident diagnosis at obstetric, emergency department or hospital encounter	EHR data extraction	Post-delivery
Infant outcomes			
Birth weight	Low birth weight (Weight at birth ≤2500 g (5.5lbs)); Macrosomia (Weight at birth ≥4500 g (9.9lbs) [60]	EHR data extraction	Post-delivery
Preterm Delivery	Delivery prior to 37 weeks gestation [60]	EHR data extraction	Post-delivery
Post delivery	Miscarriage, mode of delivery, APGARS, breastfeeding status	EHR data extraction	Post-delivery
*Nutritional*			
Food expenditures	Out-of-pocket monthly food expenditures [61]	Survey	0, 3, 6
Dietary intake	National Cancer Institute Fruit and Vegetable Screener	Survey	0, 3, 6
Food consumption diaries	Diet adherence (MTM only)	Participant report	Daily
*Psychological*			
Depressive symptoms	Patient Health Questionnaire-9 (PHQ-9) [62,63]	EHR data extraction	0, 3, 6
Stress	Perceived stress scale [64]	Survey	0, 3, 6
*Compensatory*			
Healthcare use	Number of prenatal visits, missed appointments, emergency department use, hospitalization	EHR data extraction	0, 3, 6
*Covariates*			
Demographics	Age, race, ethnicity, sex, insurance status	Survey	0
Clinical characteristics	Pre-existing maternal comorbidities (e.g., Type 2 diabetes), gestational age at first visit, initial body-mass index, smoking status, preferred language	EHR data extraction	0, 6
Health-related social needs	Housing stability, transportation barriers [16]	EHR data extraction	0, 3, 6
Socioeconomic characteristics	Education, marital status, household size, income	Survey	0

**Table 3. T3:** Embedded adaptive interventions.

Intervention	First-stage intervention	Status at end of first-stage	Second-stage intervention
1	WIC referral	Improvement	–
		Suboptimal improvement	Produce Rx
2	WIC referral	Improvement	–
		Suboptimal improvement	MTM
3	WIC referral + navigation	Improvement	–
		Sub-optimal improvement	Produce Rx
4	WIC referral + navigation	Improvement	–

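### For the Aim 1 comparison of FSSM between first-stage arms, the article names only a two-sample t-test; adjusting for the baseline FSSM already collected would be more precise at no cost

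*Protocol article*

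**What the plan says.** Protocol article, section 2.3 (Overall study design): Aim 1 is to establish whether recruitment is feasible and which first-stage intervention is potentially more effective in reducing food insecurity. Table 2 lists the 10-item FSSM under the primary outcomes for Aims 1 and 2, measured at months 0, 3 and 6.

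Section 2.9 (Statistical analysis), Aim 1: the change in food insecurity and in other outcomes will be assessed from data at baseline and 3 months. The article then remarks, while saying that detecting a difference is neither the goal nor expected, that 60 participants give power of 0.9 for arms that differ by 2 points (SD 2.0) at the 5 % level, "assuming up to a 25 % loss to follow-up (22 participants per group) using a two-sample *t*-test". No other between-arm method is given for Aim 1, and baseline FSSM as a covariate is neither specified nor excluded.

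Section 2.9, Aim 2: for change over time across the four embedded adaptive interventions, "piecewise (segmented) marginal mean regression models (fit using generalized estimating equations (GEE)) will be used", with a method reference. The fit is to inform the variance and correlation estimates for the future SMART.

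**The concern.** The first-stage contrast is one of the two questions that section 2.3 sets for the definitive trial, and preliminary effectiveness estimates are a stated objective of the pilot. With about 22 evaluable participants per arm, the interval around that contrast will be wide. Using the baseline score only through a difference, or not at all, makes it wider than it need be.

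There is also a planning consequence. Section 2.8 says that the pilot will supply variance estimates for the next sample size calculation. If the definitive trial adjusts for baseline, it needs the residual variance after adjustment and the baseline-to-follow-up correlation. The SD of a change score or of a 3-month score does not provide these alone. The article does not say which of those two quantities its SD of 2.0 describes.

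**Working it through.** **Inputs from section 2.9:** difference 2 points, SD 2.0, alpha 5 % (sidedness not stated), 22 per group after 25 % loss, power 0.9. **Assumed, because the article gives no figure:** correlation ρ between baseline and 3-month FSSM of 0.3, 0.5 or 0.7, and equal variance σ² at the two times.

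**Step 1: reproduce the stated power.**
- Noncentrality = 2 / (2.0 × √(2/22)) = 2 / 0.603 = 3.317, with 42 degrees of freedom.
- Two-sided 5 % power from the noncentral t distribution is 0.900. The normal approximation gives 0.913. A one-sided test would give 0.947 and does not match.
- 22 / 0.75 = 29.3, so 30 per arm and 60 in total.

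The stated figure is correct for whichever outcome has the SD of 2.0.

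**Step 2: variance per participant of the three analyses, in units of σ².**
- 3-month score alone: 1
- Change score: 2(1 − ρ)
- 3-month score adjusted for baseline: 1 − ρ²

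The ratio of change score to adjusted is 2(1 − ρ)/(1 − ρ²) = 2/(1 + ρ). The ratio of 3-month score to adjusted is 1/(1 − ρ²).

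| ρ (assumed) | 3-month score | Change | Adjusted | Change ÷ adjusted | 3-month score ÷ adjusted |
|---|---|---|---|---|---|
| 0.3 | 1 | 1.4 | 0.91 | 1.54 | 1.10 |
| 0.5 | 1 | 1.0 | 0.75 | 1.33 | 1.33 |
| 0.7 | 1 | 0.6 | 0.51 | 1.18 | 1.96 |

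The adjusted analysis has the smallest variance in every row. Neither t-test is uniformly better than the other: change is worse than the 3-month score at ρ = 0.3, equal at 0.5 and better at 0.7. Adjustment removes the need to choose.

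**Step 3: power with adjustment, 22 per group, 41 degrees of freedom, against 0.900 unadjusted.**
- If 2.0 is the SD of the 3-month score (residual SD 2.0 × √(1 − ρ²)): 0.924, 0.962 and 0.995 at ρ = 0.3, 0.5 and 0.7.
- If 2.0 is the SD of the change (residual SD 2.0 × √((1 + ρ)/2)): 0.980, 0.962 and 0.940.
- If ρ were 0 and 2.0 is the SD of the 3-month score: 0.899, so the covariate costs almost nothing when it does not help.

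**Step 4: the conditional Aim 2 calculation.** With 1:1 allocation at each stage, the assignment probability is 1/2 for a responder and 1/2 × 1/2 = 1/4 for a re-randomized non-responder, so the inverse-probability weights are 2 and 4. Suppose responders were counted under both embedded interventions of their arm and pooled without weights. At the article's 40 % response:
- Responder share = 0.4 / (0.4 + 0.6/2) = 0.571 instead of 0.40.
- Non-responder share = 0.429 instead of 0.60, so the within-arm Produce Rx versus MTM contrast is multiplied by 0.429/0.600 = 0.71 (0.77 at 30 % response, 0.67 at 50 %).
- Weights 2 and 4 restore the share: (0.4 × 2) / (0.4 × 2 + 0.3 × 4) = 0.40.

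If instead each responder were counted under only one of the two interventions, split evenly, the unweighted share would be 0.2 / (0.2 + 0.3) = 0.40, with no over-representation.

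**The case against.** On Aim 1, the strongest reply is that the t-test belongs to a power remark about something described as not the goal, so it does not fix the analysis. A change outcome already uses the baseline score. Both comparisons are unbiased under randomization, the stated power is right, and the trial is a feasibility pilot that section 3 says is not powered for differences between arms. The gain also rests on assumed correlations. All of this stands, and it limits the point to precision. A reader might infer that an unadjusted t-test is the fixed Aim 1 analysis; the text goes no further than naming no other between-arm method. What the reply does not remove is that the article sets out to learn which first-stage intervention looks better, and that a more precise estimate is available from data it already collects.

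On Aim 2, a reader might infer that the GEE will be fitted without weights and that the embedded means are therefore biased toward responders. The article does not support that. It does not prescribe an unweighted fit, and it cites a method reference that is not at hand. Table 3 places the improvement row under each of the four embedded interventions, so responders are already shared between the two in their arm. Weights, replication and the variance estimator are details that a condensed article commonly leaves to the full protocol or SAP. The 57 % share and the shrinkage to 71 % arise only if shared responders are pooled without weights. A direct Produce Rx versus MTM comparison among non-responders needs no such weights at all.

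**Conclusion.** The point holds as a matter of efficiency in Aim 1. The one between-arm method named does not adjust for baseline FSSM. Relative to baseline-adjusted regression, the variance of the first-stage contrast is about 1.18 to 1.54 times as large with a change-score t-test, and about 1.10 to 1.96 times as large with a t-test on 3-month scores. These ranges assume a correlation of 0.3 to 0.7, equal variances at baseline and 3 months, and a linear relation between the two scores. There is no bias and no wrong figure: the power of 0.9 reproduces. Because the primary questions are feasibility proportions, this is a free improvement and does not threaten the trial's conclusions.

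The Aim 2 weighting is a conditional caution only. The shrinkage to about 71 % at 40 % response describes one way the model could be implemented wrongly, not what the article says will be done.

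**What to change.** In section 2.9, or in the SAP, state that the first-stage arms will be compared on 3-month FSSM by linear regression with baseline FSSM as a covariate, with the estimate and 95 % confidence interval reported. Report the residual variance and the baseline-to-3-month correlation as planning inputs for the full SMART, and say whether the SD of 2.0 refers to the 3-month score or to the change. As a safeguard, add one sentence confirming how the Aim 2 GEE treats responders: if they are replicated under both embedded interventions of their arm, with weights 2 (responders) and 4 (re-randomized non-responders) and participant-clustered robust standard errors.

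The cost is wording only. No new data, visits or participants are needed. Section 3 expects enrollment to finish by the end of 2026 and results in fall 2027, so the text can be settled before analysis.

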## Discussion

3.

We began recruitment June 2025 and anticipate completing enrollment by the end of 2026. We will begin qualitative data collection after a sufficient number of participants complete the 6-month intervention period (winter 2025/2026). Final results are anticipated in fall 2027. There are several limitations to this study that should be acknowledged. First, this is a pilot study, so the study is not powered to detect differences in the intervention arms or the embedded adaptive interventions. Second, this study will be conducted at obstetric clinics from one health system, so the results may not be generalizable to other settings. Third, although we have taken steps to minimize participant burden, research participation is inherently burdensome, and patients who participate may differ from populations who are pregnant and living with FI.

FI during pregnancy has been associated with numerous negative maternal and infant health outcomes [9–13]. Increasingly, studies are testing Food is Medicine interventions to assist pregnant individuals from food-insecure households as part of routine clinical care [22,23,57]. The interventions tested in these studies have shown promise in reducing FI and improving maternal and infant health outcomes and included referring patients to nutrition support programs, providing Produce Rx, and delivering MTM. However, this study will be the first to develop and test an adaptive intervention to address FI in pregnant patients. An adaptive FI intervention could reduce costs and burden to both participants and clinicians by providing no more treatment than is needed for food-insecure participants who respond to a less intensive approach and redirecting the saved resources to participants who need a more intensive approach. An adaptive FI intervention could also be more efficacious in improving maternal and child health outcomes by providing additional support to patients most in need. Given the growing interest among healthcare systems and insurers in integrating FI interventions in clinical care, an efficacious adaptive intervention could be broadly disseminated across healthcare settings.

## Figures and Tables

**Fig. 1. F1:**
[figure not shown]
Overall study design. We will conduct a single site pilot sequential multiple assignment randomized trial (SMART). Patients (N = 60) who are pregnant and food insecure will be randomized to receive one of 2 interventions in Stage 1:1) EHR referral to WIG or 2) EHR WIC referral + care navigation. We will follow up all participants at 6 months Participants who do not have ≥2 point decreased in food insecurity at 3 months (suboptimal improvement) will be re-randomized to one of 2 interventions in Stage 2: 1) Produce Rx or 2) MTM. We will follow up all participants at 6 months. EHR-electronic health record; MTM-medically tailored meals; Produce Rx-produce prescriptions; WIC-Special Supplemental Nutrition Assistance Program for Women, Infants, and Children.

**Table 1. T1:** Inclusion and exclusion criteria.

Inclusion	Exclusion
1. ≥18 years of age	1. Planning on moving out of the area within 6 months
2. Confirmed viable pregnancy by their obstetrician or midwife based on urine pregnancy test and ultrasound	2. Severe cognitive impairment or major psychiatric illness that prevents consent or serious medical condition which either limits life expectancy or requires active management (e.g., certain cancers)
3. Experience FI based on the 2-item Hunger Vital Sign^™^	3. Lack safe, stable residence or the ability to store the MTM
4. Speaks English or Spanish	4. Lack of a telephone
5. Not currently enrolled in WIC	5. Severe food allergy or require a specialized diet (e.g., Celiac)
6. First trimester at the time of the initial prenatal visit	

**Table 2. T2:** Study outcomes and measures.

Measure	Potential sample measures and citations	Data source	Month
Primary outcomes			
Feasibility of recruitment/proportion recruited (**Aim 1**)	Proportion of eligible patients who enroll	Study logs	0
Feasibility of retention/proportion retained (**Aim 2**)	Proportion of participants who complete follow-up data collection	Study logs	6
Feasibility of re-randomization/proportion rerandomized (**Aim 2**)	Proportion of eligible participants who are re-randomized to stage 2 interventions	Study logs	3
Food insecurity (**Aim 1 and 2**)	10-item USDA FSSM with 30-day reference period [7]	Survey	0, 3, 6
Maternal outcomes			
Gestational Diabetes Mellitus (GDM)	One-step oral glucose tolerance test shows ≥2 abnormal values consistent with diagnostic criteria for GDM [58], or incident diagnosis of GDM added during pregnancy	EHR data extraction	6
Glucose Homeostasis (Hypo or Hyperglycemia, glucose variability)	14-day monitoring of glucose for episodes of hypo/hyperglycemia and glucose coefficient of variation	CGM	0, 6
Excess Gestational Weight Gain	If pre-pregnancy BMI ≥30, gaining ≥20lbs; if BMI 25–29.9, gaining ≥25lbs; if BMI <25, gaining ≥35lbs [59]	EHR data extraction	Post-delivery
Pre-eclampsia	Incident diagnosis at obstetric, emergency department or hospital encounter	EHR data extraction	Post-delivery
Infant outcomes			
Birth weight	Low birth weight (Weight at birth ≤2500 g (5.5lbs)); Macrosomia (Weight at birth ≥4500 g (9.9lbs) [60]	EHR data extraction	Post-delivery
Preterm Delivery	Delivery prior to 37 weeks gestation [60]	EHR data extraction	Post-delivery
Post delivery	Miscarriage, mode of delivery, APGARS, breastfeeding status	EHR data extraction	Post-delivery
*Nutritional*			
Food expenditures	Out-of-pocket monthly food expenditures [61]	Survey	0, 3, 6
Dietary intake	National Cancer Institute Fruit and Vegetable Screener	Survey	0, 3, 6
Food consumption diaries	Diet adherence (MTM only)	Participant report	Daily
*Psychological*			
Depressive symptoms	Patient Health Questionnaire-9 (PHQ-9) [62,63]	EHR data extraction	0, 3, 6
Stress	Perceived stress scale [64]	Survey	0, 3, 6
*Compensatory*			
Healthcare use	Number of prenatal visits, missed appointments, emergency department use, hospitalization	EHR data extraction	0, 3, 6
*Covariates*			
Demographics	Age, race, ethnicity, sex, insurance status	Survey	0
Clinical characteristics	Pre-existing maternal comorbidities (e.g., Type 2 diabetes), gestational age at first visit, initial body-mass index, smoking status, preferred language	EHR data extraction	0, 6
Health-related social needs	Housing stability, transportation barriers [16]	EHR data extraction	0, 3, 6
Socioeconomic characteristics	Education, marital status, household size, income	Survey	0

**Table 3. T3:** Embedded adaptive interventions.

Intervention	First-stage intervention	Status at end of first-stage	Second-stage intervention
1	WIC referral	Improvement	–
		Suboptimal improvement	Produce Rx
2	WIC referral	Improvement	–
		Suboptimal improvement	MTM
3	WIC referral + navigation	Improvement	–
		Sub-optimal improvement	Produce Rx
4	WIC referral + navigation	Improvement	–
		Sub-optimal improvement	MTM

MTM-medically tailored meals; Produce Rx-produce prescriptions; WIC-Special Supplemental Nutrition Assistance Program for Women, Infants, and Children.

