In Aim 1, we will determine the feasibility of recruitment and which first-stage intervention is potentially more effective in reducing FI. In Aim 2, we will evaluate the feasibility of re-randomization, data collection, and retention and compare preliminary estimates of change in FI of providing Produce Rx versus MTM among participants who did not respond to the first-stage intervention. In Aim 3, we will advance our understanding of how, why, and under what circumstances participants achieved improvements to the interventions. Participants will engage in the interventions for up to 6 months, and we will follow all participants to after they have delivered. A 6-month intervention period was selected in keeping with similar FI studies [22,23]. As secondary outcomes, we will evaluate maternal and infant outcomes (Table 2) including the number of participants who are diagnosed with gestational diabetes, have excess gestational weight gain, pre-eclampsia, infant birth weight, and pre/post-term delivery based on data extraction from the EHR. Based on the impact of FI on health conceptual framework, we will also assess changes in nutritional, psychological, and compensatory pathways from baseline to 6 months [31–33]. As an exploratory aim, participants will wear a continuous glucose monitor (CGM) at 2 time points: baseline (first 2 weeks) and at 6-month follow up.

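### Table 2 defines birth weight only by two sparse cut-offs; adding the weight in grams would recover about half or more of the information on a mean shift at almost no cost

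*Protocol article*

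**What the plan says.** Section 2.3 (Overall study design) introduces the secondary outcomes by reference to Table 2: "we will evaluate maternal and infant outcomes (Table 2) including the number of participants who are diagnosed with gestational diabetes". The list goes on to "pre-eclampsia, infant birth weight, and pre/post-term delivery based on data extraction from the EHR".

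Table 2, under infant outcomes, gives these measures, all extracted from the EHR after delivery:

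- Birth weight: "Low birth weight (Weight at birth ≤2500 g (5.5lbs)); Macrosomia (Weight at birth ≥4500 g (9.9lbs".
- Preterm delivery: "Delivery prior to 37 weeks gestation".
- A row labelled post delivery: "Miscarriage, mode of delivery, APGARS, breastfeeding status".

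The measures column is headed "Potential sample measures and citations". No row gives birth weight in grams, gestational age at delivery in weeks, or a post-term threshold.

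Section 2.9 (Statistical analysis) adds one general sentence: "We will summarize the distribution of FI and secondary outcomes at baseline, 3 months, and 6 months". For food insecurity, by contrast, Section 2.6 fixes the scale: continuous in the primary analysis, binary in secondary analyses.

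**The concern.** Birth weight is a measured quantity. Reduced to two tail indicators, every infant strictly between 2500 g and 4500 g is treated alike, and that is nearly all of them. In a sample this small each indicator rests on a handful of events, and the macrosomia count may well be zero.

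Two things are at stake. The first is the precision of any preliminary comparison of birth weight between arms. The second is planning information: a count at a cut-off gives no SD, so a later trial that wished to use mean birth weight could not take its variance from this pilot's reported results. Neither loss is forced by data collection, because the cut-offs cannot be applied without the weight in grams.

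**Working it through.** **The plan's own figure.** The article states no precision or power for birth weight or delivery timing. Its only power figure concerns food insecurity (difference 2, SD 2.0, 22 per group, alpha 5%, power 0.9; Section 2.9). It reproduces: the noncentrality is 2/(2·√(2/22)) = 3.32, and a two-sided noncentral t with 42 df gives 0.900. It has no bearing on this point.

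**Inputs.** From the article: cut-offs 2500 g and 4500 g (Table 2); 60 enrolled and up to 25% attrition, so 60 × 0.75 = 45 (Section 2.8); 22 per group (Section 2.9). Assumed, because the article gives nothing: normal birth weights, mean μ from 3100 to 3300 g, SD σ from 450 to 600 g.

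**Formula.** Let z₁ = (2500 − μ)/σ, z₂ = (4500 − μ)/σ, p_L = Φ(z₁) and p_M = 1 − Φ(z₂). Relative to 1 for the weight in grams, the information on a small mean shift kept by the two cut-offs together is

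φ(z₁)²/p_L + (φ(z₂) − φ(z₁))²/(1 − p_L − p_M) + φ(z₂)²/p_M.

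For one cut-off alone it is φ(z)²/[p(1 − p)].

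**One case in full (μ = 3200, σ = 500).** z₁ = −1.4 and z₂ = 2.6; φ(z₁) = 0.1497 and φ(z₂) = 0.0136; p_L = 0.0808 and p_M = 0.0047. The three terms are 0.277 + 0.020 + 0.040 = 0.34.

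**Across the range** (expected events shown for 45 / 60 births):

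| μ, σ (g) | Low birth weight | Expected | Macrosomia | Expected | Kept, low only | Kept, macrosomia only | Kept, both |
|---|---|---|---|---|---|---|---|
| 3100, 450 | 9.1% | 4.1 / 5.5 | 0.09% | 0.04 / 0.06 | 0.32 | 0.011 | 0.33 |
| 3100, 600 | 15.9% | 7.1 / 9.5 | 0.98% | 0.44 / 0.59 | 0.44 | 0.071 | 0.50 |
| 3200, 500 | 8.1% | 3.6 / 4.8 | 0.47% | 0.21 / 0.28 | 0.30 | 0.040 | 0.34 |
| 3300, 450 | 3.8% | 1.7 / 2.3 | 0.38% | 0.17 / 0.23 | 0.19 | 0.034 | 0.22 |
| 3300, 600 | 9.1% | 4.1 / 5.5 | 2.28% | 1.02 / 1.37 | 0.32 | 0.131 | 0.44 |

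Over the 12 combinations examined (three means, four SDs) the two cut-offs together keep 0.22 to 0.50, a loss of 50–78%. With 60 births, 11 of the 12 combinations give fewer than one expected macrosomic infant.

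**What this means for an interval.** With 22 per arm, the 95% half-width for a mean difference from the grams is 1.96·√(2/22) = 0.59 SD. Recovering the same shift from the cut-offs alone would give between 0.59/√0.50 = 0.84 SD and 0.59/√0.22 = 1.26 SD.

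**Check by another route.** Assuming event rates directly, the single-cut-off formula gives 0.30–0.38 for low birth weight in 8–12%, and 0.07–0.12 for macrosomia in 1–2%. This agrees with the table.

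**Post-term delivery.** No calculation is possible, since the article gives neither a rate nor a threshold. Set side by side, Section 2.3 names both ends of delivery timing and Table 2 defines only the preterm end. The post-delivery row does not fill the gap.

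**The case against.** A reader might infer that Table 2 contradicts Section 2.3 on birth weight. It does not. The list in Section 2.3 opens as a count of participants and points to Table 2, so cut-offs are compatible with it, and no continuous analysis is promised.

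A reader might also infer that post-term births will never be counted. That goes too far. Section 2.3 says delivery timing will be evaluated from the EHR, and the 37-week rule needs gestational age at delivery, so post-term births could be identified. What is missing is a definition.

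Further points on the plan's side:

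- The Table 2 column heading does not claim to be exhaustive, and Section 2.9 speaks of summarising distributions, so other summaries are not excluded. This stands, and it makes the loss conditional on the cut-offs being the only analysis. But birth weight is a post-delivery outcome and that sentence names baseline, 3 and 6 months, so it does not clearly supply the missing summary.
- The variance estimates sought in Sections 2.3 and 2.8 are mainly for a future trial of food insecurity. This stands: a missing birth-weight SD defeats no stated aim.
- Sections 2.9 and the Discussion disclaim power for differences. This also stands and limits the importance. It is no reason to discard precision that costs nothing.
- Low birth weight is part of the stated rationale in the Background. That supports keeping the cut-off, not reporting it alone.

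**Conclusion.** The point holds as a criticism of efficiency. If the two cut-offs are the only birth-weight analysis, roughly half or more of the information on a mean shift is lost: about 50–78% for normal birth weights with mean 3100–3300 g and SD 450–600 g. All of these inputs are assumptions. The figure applies to a small shift of the whole distribution; an effect confined to one tail would be a different question, which the counts address. No corresponding figure was computed for gestational age at delivery.

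The documents do not support calling this an internal contradiction, an exclusion of post-term births, or a failure of the pilot's purpose. The undefined post-term outcome is a minor inconsistency. Overall this is a cheap improvement to secondary outcomes, worth making before analysis, and it does not touch the feasibility aims.

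**What to change.** In Table 2, add two continuous measures: birth weight in grams and gestational age at delivery in weeks. Report the mean difference with 95% CI, and the SD, by arm. Keep the ≤2500 g, ≥4500 g and <37-week definitions as counts. This follows the approach Section 2.6 already takes for food insecurity, continuous first and binary second.

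Do not adjust birth weight for gestational age at delivery. That variable arises after randomisation, is itself an outcome here, and may lie on the path from intervention to birth weight.

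Reconcile the two places on post-term delivery: either give it a measure in Table 2 or remove it from Section 2.3.

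The cost is small. Applying the existing cut-offs already requires both quantities from the EHR, so no new data are needed. Recruitment began in June 2025 and the trial is unblinded, so the addition should be dated and made before these outcomes are examined by arm. One downside is that a mean can hide opposite shifts in the two tails, which the retained counts would show.
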